#### Tertiary objectives

The tertiary objectives include investigations within three distinct groups of AECOPD: (1) patients with evidence of Takotsubo stunning, (2) patients without evidence of Takotsubo stunning and (3) the overall cohort, including both patients with and without Takotsubo stunning. In accordance with the secondary objectives, these analyses will also be conducted within a hypothesis-generating framework.

Concordance between echocardiography, chest X-ray and NT-proBNP in displaying signs of heart failure.Prevalence of right ventricular pathology.Prevalence of diastolic dysfunction.The association between NT-proBNP and in-hospital outcome.The association between Killip classification and in-hospital outcome.

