### Statistical plan and sample size

Inclusion is planned over approximately 3 years to estimate the cumulative incidence of Takotsubo stunning in patients hospitalised for AECOPD. The primary analysis will assess the association between a positive screening result and clinical manifestations of AHF using multivariable logistic regression. The model will adjust for relevant baseline confounders, with a significance threshold of α=0.05.

For the primary analysis, the required sample size is estimated at 150 patients, assuming a 1:10 ratio of positive to negative screening results. In previous research randomly investigating the correlation between clinical and echocardiographic signs of heart failure, clinical heart failure was present in approximately 50% of patients with echocardiographic left ventricular systolic dysfunction (LVEF <40%).^23^ Given the higher cut-off for systolic dysfunction in CATCH (LVEF <50%) and inclusion of newly detected RWMA as positive screening (ie, also in absence of reduced LVEF), together with the exclusion of patients with prior type 1 myocardial infarction or known persistent systolic dysfunction, we conservatively estimate the proportion of clinical heart failure in the positive screening group to approximately 30%. Accordingly, our sample provides 80% power to detect a difference in the incidence of clinical signs of AHF between the groups, assuming 30% in the positive screening group and 5% in the negative screening group with α=0.05.

Secondary and tertiary outcomes will be analysed using linear regression for continuous outcomes and logistic regression for dichotomous outcomes, in both unadjusted and adjusted models. A Cox proportional hazards model adjusted for baseline confounders will be applied to analyse 1-year mortality. These analyses are considered explanatory or hypothesis generating. Results will be reported as effect estimates with 95% CIs and unadjusted p values, with false discovery rate correction applied to account for multiple comparisons.^24^

Unadjusted and adjusted analyses (including covariates age and sex) will be presented as separate models. A sample size of 150 patients, with an assumed 1:10 ratio of positive to negative screening results, translates to a total number of 15 events. Given the relatively low number of expected events, all further adjustment will include only clinically meaningful covariates and will be presented as separate models.

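### Age- and sex-adjusted logistic models inside a Takotsubo group of at most about 14 patients will often have no finite estimate when the in-hospital outcome is uncommon

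*Protocol article*

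**What the plan says.** The protocol's Tertiary objectives section sets its investigations inside three groups, the first being "1) patients with evidence of Takotsubo stunning". Its topics include "The association between NT-proBNP and in-hospital outcome" and the same association for Killip class.

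The section Statistical plan and sample size assigns secondary and tertiary outcomes to linear regression if continuous and to "logistic regression for dichotomous outcomes, in both unadjusted and adjusted models" if dichotomous. The adjusted model contains age and sex; any further covariates go into separate models.

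On size, the same section says that "the required sample size is estimated at 150 patients, assuming a 1:10 ratio of positive to negative screening results", and that this "translates to a total number of 15 events". Those 15 are screening-positive patients, not outcome events.

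The Cardiac screening section narrows the group further. Only screening-positive patients with reversible dysfunction and no alternative cause become cases; those with persistent dysfunction leave the analysis.

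**The concern.** Most in-hospital outcomes listed under Secondary outcomes are yes/no: MACE, intensive care admission, death, respiratory failure. The adjusted model has four parameters (intercept, marker, age, sex) and would be fitted to at most about 14 patients with perhaps one to four events.

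In such data some combination of the covariates often splits events from non-events perfectly, or almost so. The likelihood then has no finite maximum: the odds ratio drifts to zero or infinity, and the software's standard error reflects where the iterations stopped. This differs from a wide confidence interval, which the hypothesis-generating label would excuse.

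The plan recognises that numbers are low, but its only safeguard limits covariates beyond age and sex. At stake is whether the tertiary results for the group of most interest can be reported as promised, as effect estimates with 95% CIs.

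**Working it through.** **1. The plan's own figure.** Inputs: 150 patients, ratio 1:10, and, in the plan's words, "assuming 30% in the positive screening group and 5% in the negative screening group with α=0.05". Group sizes are 150/11 = 13.64 and 136.36. The pooled proportion is (13.64 × 0.30 + 136.36 × 0.05)/150 = 0.0727. The standard error is 0.0738 under the null and 0.1255 under the alternative. Then z = (0.25 − 1.96 × 0.0738)/0.1255 = 0.84, which gives power 0.80. The stated 150 patients and 80% reproduce (two-sided, pooled variance, no continuity correction).

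**2. Size of the Takotsubo group.** 13.6 rounds to 14; the plan says 15. Either is the expected ceiling, before non-reversible cases and alternative causes are removed. The protocol does not say how many that will be.

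**3. Events within the group.** The protocol gives no rates for the in-hospital outcomes of these models, so 5-30% is an assumed range. Its 30% for clinical heart failure among screening-positives lies at the top. With n = 14, expected events are 14p and the chance of no event is (1 − p)^14.

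**4. Simulation, n = 14.** Each data set has a standard normal marker and age, a binary sex and no true association. A linear program tests for complete or quasi-complete separation. Data sets with no event count as having no finite estimate, and are removed in the columns marked "given events".

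| Outcome rate | Expected events | No event | Adjusted NT-proBNP, 55% female: no finite estimate | Same, given events | Adjusted, 90% female | Unadjusted, given events |
|---|---|---|---|---|---|---|
| 5% | 0.7 | 49% | 93% | 85% | about 90% | about 10% |
| 10% | 1.4 | 23% | 78% | 72% | about 80% | about 6% |
| 20% | 2.8 | 4% | 47% | 45% | about 68% | about 3% |
| 30% | 4.2 | 1% | 27% | 26% | about 60% | about 1% |

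With 600 to 1,500 data sets per cell, the Monte Carlo standard error is at most √(0.25/600) = 2 percentage points. Repeat runs agree within a few points (the last 90%-female cell ranged from 55% to 60%). A true effect of one log-odds unit per SD of the marker changes little: 89%, 76%, 46% and 31% for the four rates at 60% female.

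**5. Sex mix.** The Introduction says that more than 90% of Takotsubo patients are women. With 90% women the failure rate stays above one half, but part of this is separation on sex alone. The NT-proBNP coefficient itself is then non-finite in 71%, 43%, 19% and 8% at the four rates.

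**6. Killip class as exposure.** With Killip class above I in 30% of the group and balanced sexes, the adjusted model fails in 97%, 88%, 67% and 46%.

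**7. Overall cohort (n = 150).** The adjusted NT-proBNP model fails in at most 6%. The Killip model, simulated with 5% above class I, still fails in 70%, 45%, 19% and 10%. So moving to the full cohort nearly cures the first by itself, while the second also needs penalisation.

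**The case against.** The strongest reply is that this belongs in a statistical analysis plan that is not shown. The regression sentence is generic, it does not require Wald intervals, and Firth-penalised logistic regression is still logistic regression. Three of the five tertiary topics concern concordance or prevalence, so the sentence plainly does not apply to every topic in every group. In-hospital outcome is not defined there, and length of stay would be analysed by linear regression, where separation cannot occur. Non-convergence would also be noticed at analysis.

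Much of this stands and limits the point. It does not remove it: for the two association topics and the mainly dichotomous in-hospital outcomes, the article names both the group and the model. Unqualified logistic regression is ordinarily read as maximum likelihood.

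A reader might infer more than the protocol supports:

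- *That the whole method fails in this group.* The unadjusted model, which is half of what is prescribed, separates in only about 3-10% of data sets with events at rates of 5-20%.
- *That failure is the usual result whatever the outcome.* With near-balanced sexes it is below one half at rates of 20-30%. At 5%, about half of all data sets have no event, which no method could model.
- *That the group will be about 7 patients.* This assumes that half the positives are reversible, a figure the protocol does not give.
- *That invalid p values damage the false discovery rate correction.* In 223 separated data sets (n = 14, rate 10%) the smallest Wald p value for the marker was 0.17 and the median 0.998. Such values make a correction slightly more conservative at most, and the article does not define the family.

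**Conclusion.** The point holds for the adjusted logistic models of dichotomous in-hospital outcomes within the Takotsubo group, mainly for uncommon outcomes. At n = 14 and rates of 5-10%, about four in five or more adjusted NT-proBNP fits would have no finite estimate; Killip class is somewhat worse. At 20-30% the answer depends on the sex mix.

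The ceiling of about 14 follows from the protocol's own ratio. The outcome rates, the covariate distributions and the 55% female figure are assumptions. The 90% figure approximates the protocol's description of Takotsubo syndrome in general, not of this cohort.

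The importance is low: the analyses are tertiary and declared hypothesis generating, and neither the primary analysis nor the sample size is affected.

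**What to change.** In Statistical plan and sample size, or in the statistical analysis plan, add wording such as: within the Takotsubo group, dichotomous in-hospital outcomes are reported descriptively, as counts with exact 95% CIs, with at most an unadjusted Firth-penalised odds ratio and its profile-likelihood CI; the adjusted models relating NT-proBNP and Killip class to in-hospital outcome are fitted in the overall cohort with Firth penalisation.

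The cost is a change of wording. The downside is that no adjusted odds ratio is reported for the case group alone. The Study status section reports 56 of 150 patients enrolled and analysis after inclusion ends, so the change can still be pre-specified.

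### The stated 15 events is roughly the count of screening-positive patients; the plan's own rates imply about 11 AHF events for the primary model

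*Protocol article*

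**What the plan says.** Everything here is in the protocol article, section *Statistical plan and sample size*, unless stated otherwise.

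- The primary analysis is a multivariable logistic regression relating a positive screening echocardiogram (exposure) to clinical AHF (outcome). The *Outcomes* section defines AHF as Killip class above I.
- Sample size: "For the primary analysis, the required sample size is estimated at 150 patients, assuming a 1:10 ratio of positive to negative screening results".
- AHF rates: "assuming 30% in the positive screening group and 5% in the negative screening group with α=0.05", for which the section claims 80% power.
- Event count: 150 patients, "with an assumed 1:10 ratio of positive to negative screening results, translates to a total number of 15 events".
- Use made of that count: "Given the relatively low number of expected events, all further adjustment will include only clinically meaningful covariates". These further models are to be shown separately. Age and sex are the only covariates named, and no number is given for the others.

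**The concern.** How many covariates a logistic model can carry depends on how many patients have the outcome, not on how many have the exposure. The sentence giving 15 events starts from the total and the screening ratio and never applies the AHF rates stated two paragraphs earlier. It therefore appears to count screening-positive patients and label them events.

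The number has a job: the next sentence gives the low event count as the ground for restricting adjustment. If the true expectation is lower, an analyst who sizes the further-adjusted models on 15 will put in more covariates than the data can support. Maximum-likelihood odds ratios then drift away from the null.

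**Working it through.** **Inputs** (all from *Statistical plan and sample size*): N = 150; ratio of positives to negatives 1:10; AHF 30% in positives and 5% in negatives; α = 0.05, taken as two-sided because that reproduces the stated power.

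**1. The plan's power.** Positives: 150/11 = 13.64. Negatives: 136.36. Overall AHF rate: 10.91/150 = 0.0727 (events from step 3).
- Null standard error: √[0.0727 × 0.9273 × (1/13.64 + 1/136.36)] = 0.0738.
- Alternative standard error: √[0.30 × 0.70/13.64 + 0.05 × 0.95/136.36] = 0.1255.
- Power: Φ[(0.25 − 1.96 × 0.0738)/0.1255] = Φ(0.84) = 0.80.

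The stated 80% reproduces without using the figure of 15.

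**2. Where 15 comes from.** 15 = 10% of 150. That is a 1:9 split of screening results; a strict 1:10 split gives 13.6. Either way it is a number of exposed patients.

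**3. Expected AHF events.** 0.30 × 13.64 + 0.05 × 136.36 = 4.09 + 6.82 = 10.9. Other splits hardly move it:

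| Positive / negative | Expected AHF events |
|---|---|
| 13 / 137 | 10.75 |
| 14 / 136 | 11.0 |
| 15 / 135 | 11.25 |
| 15 / 150 (N = 165) | 12.0 |

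Overstatement: 15/10.91 = 1.375, about 37%. With 14 and 136 patients, the number of events has median 11 and a 95% range of 5 to 17; the chance of 15 or more is 0.13.

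**4. Events per slope.** Unadjusted: 10.9. Exposure, age and sex: 10.9/3 = 3.6, against 15/3 = 5.0 on the stated count.

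**5. Consequence for the estimate.** Simulation of 3,000 trials per row, 14 positives and 136 negatives, ordinary maximum likelihood. The covariates are unrelated to exposure and outcome. True odds ratio: (0.30/0.70)/(0.05/0.95) = 8.14, log 2.10. Means exclude the few runs with extreme exposure estimates (absolute log odds ratio of 8 or more).

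| Covariates beside exposure | Mean log OR | Wald power | Wald type I error |
|---|---|---|---|
| 0 | 2.11 | 0.80 | 0.039 |
| 2 | 2.19 | 0.79 | 0.032 |
| 4 | 2.28 | 0.78 | 0.037 |
| 6 | 2.37 | 0.77 | 0.034 |

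Only the first two rows correspond to models the article names. The rows with 4 and 6 covariates are illustrations, since the article gives no number. In a separate simulation, Firth's method with 2 covariates had mean log odds ratio 2.07, and it stayed at 2.09 to 2.10 with 5 and 8.

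**6. No exposed patient with AHF.** Ordinary maximum likelihood then has no finite odds ratio. At the design rates the probability is 0.7^14 = 0.7%. If AHF is equally common in both groups (7.3%), it is 0.927^14 = 35%.

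**The case against.** The strongest reply is that nothing stated turns on the 15. It does not enter the sample size or the power. The article draws no covariate count or events-per-variable rule from it, only the conclusion that events are few and adjustment must be restrained, and at 11 that conclusion is stronger still. This stands, and it is why the point is moderate. It does not make the figure right: it is the stated ground for limiting adjustment, and it is too large by more than a third.

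A second reply is that events means Takotsubo-stunning cases, the first primary outcome. But that outcome is a cumulative incidence, and the sentence limits adjustment in a regression whose outcome is AHF. Nor are all positives stunning cases: under *Cardiac screening*, positives with persistent dysfunction are excluded from analysis.

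A reader might go further and infer that the planned models are overfitted. The documents do not support that. The unadjusted model has about 11 events for one slope. With age and sex the bias is modest (2.19 against 2.10) and type I error is not inflated. Wide scatter in the odds ratio comes mostly from having 14 exposed patients: the unadjusted estimate exceeds twice the truth in 17% of trials by exact enumeration. With two covariates the share is 22% by maximum likelihood and 16% by Firth (2,000 runs).

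A reader might also infer that no model is designated to decide at 0.05. The article does call the primary analysis multivariable and adjusted. The exact confounder list, like the choice of estimator, is ordinary content for an analysis plan that is not shown.

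**Conclusion.** The event count is wrong as written. On the plan's own ratio and rates, the primary model expects about 11 AHF events, not 15. The stated figure overstates the information by about 37%, and events per slope in the age-and-sex model fall from 5 to 3.6. This rests only on the article's assumptions of 30%, 5% and 1:10, and holds for any nearby split of 150. The actual number could fall anywhere from about 5 to 17.

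The risk of an inflated odds ratio rises with each added covariate; it is not established as a serious fault of the models actually named. N = 150 and 80% power are untouched. The gap between 13.6 and 15 exposed patients is a rounding-size slip (one in eleven against one in ten) and would not merit comment alone. Severity: moderate.

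**What to change.** 1. Replace the 15 events with: *about 14 screening-positive patients and about 11 AHF events (about 4 in positives and 7 in negatives)*.
2. Set the limit on further adjustment from about 11 events. Keep exposure, age and sex as the main adjusted model; label any further-adjusted models supportive and keep them small.
3. Fit the models with a sparse-data method, such as Firth penalised logistic regression with profile penalised-likelihood intervals. This also gives a finite estimate if no exposed patient has AHF. Other sparse-data methods would serve.

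The cost is one corrected figure, fewer covariates per model and a standard software option. Power should be confirmed for whichever test is adopted: in the simulation above, the ordinary likelihood-ratio test with two covariates had power of about 0.75, against 0.79 for the Wald test. *Study status* reports 56 of 150 patients enrolled and analysis only after inclusion ends, so the change can be made before any results are analysed.

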### Study status

Inclusion started on September 2024 and to date (April 2026), 56 patients have been enrolled (of 150 patients intended for the primary analysis). Analysis is planned after end of inclusion.

### Scientific and clinical importance

The risk of both fatal and non-fatal cardiovascular disease is a major concern in patients with COPD, especially after a hospitalisation for AECOPD. This established excess cardiovascular risk after AECOPD is incompletely understood. A link seems to exist between AECOPD and Takotsubo stunning, which could be a contributing mechanistic explanation, supported by previous literature.^12 12^,^15 25^ Leading authors in the field of TS have specifically advocated further investigations of this association.^2^

This study is clinically relevant for two main reasons: (1) the cardiac condition may be masked by the respiratory symptoms and the clinical signs of AECOPD, leading to delayed or missed diagnosis of the cardiac component, (2) Takotsubo stunning with cardiac dysfunction may further exacerbate the patient’s condition, leading to prolonged time to recovery due to concomitant untreated AHF and an increased risk of severe cardiac complications.^2 5 15^

Another important aspect is the treatment for AECOPD, which may include treatment with high doses of beta-2 agonists. Catecholamines are part of the pathophysiological cause of Takotsubo stunning, and catecholaminergic drugs may further aggravate Takotsubo stunning. In fact, beta-2 agonists specifically have been shown to likely trigger Takotsubo stunning. Therefore, the routine treatment for AECOPD may be associated with a risk of harming patients with concomitant AECOPD and Takotsubo stunning.^5 6^

If successful, the CATCH study may improve the quality of care and outcomes for patients with AECOPD by highlighting the need to address AECOPD as a cardiopulmonary syndrome, rather than a purely pulmonary condition. In addition, the study may help guide optimisation of treatment strategies for AECOPD, for example, by providing insights into settings in which excessive use of beta-2 agonists may be inappropriate.

### Patient and public involvement

This study originates from the person-centred care context at Sahlgrenska University Hospital, where patient perspectives are a central part of everyday clinical work, in accordance with the hospital’s core value explicitly phrased in the hospital policy: ‘For the patient, with the patient’. Through ongoing dialogue with patients, previously unrecognised clinical needs and gaps in existing knowledge were identified, which influenced the study objectives. This is particularly relevant since the majority of investigators and collaborators in this study are also treating physicians for the included patients. Patients and the public were not otherwise involved in the study design or conduct.

Results of the study will be disseminated through scientific publications and presentations. In addition, findings will be communicated in formats accessible to patients and the public, including plain language summaries and dissemination through relevant clinical settings where patients receive care.

## Ethics and dissemination

A cooperation with Gothia Forum (regional unit for clinical research and trial support in Region Västra Götaland, Sweden) is established for monitoring/quality assurance. The CATCH study adheres to the principles of Good Clinical Practice and follows the Declaration of Helsinki. All participants provided verbal and written IC prior to inclusion. Study data is handled in accordance with applicable data protection regulations and stored on secure, access-controlled servers within Sahlgrenska University Hospital and Sahlgrenska Academy (University of Gothenburg, Sweden). The CATCH study is registered at ClinicalTrials.gov (NCT06597331), and findings from the study will be disseminated through peer-reviewed publications and conference presentations. No identifying information will be published.

## Data Availability

No data are available.
